### Randomization

With an average of five participants per intervention group, a total of ten intervention groups for both adolescents and parents will be given. Interventions are organized at different time points (in four to six cohorts, dependent on inclusion rates). In each cohort, participants are randomly allocated to the conditions resulting in an equal number of participants in the intervention and waitlist control condition. The randomization is carried out by an independent IT worker from a company for e-health development who administers the website for *Op Koers Online*, using block randomization software.

### Sample size

Earlier studies on the effectiveness of *Op Koers* and comparable effect studies showed effects of medium size [32, 53]. Based on a design with four repeated measurements and a within subject correlation of .5, 84 adolescents and 84 parents are needed – 42 in each condition – to detect an intervention effect of medium size (d = .05) over time, at a two-sided .05 significance level and 80% power. Taking into account a dropout of 15% over time, 96 adolescents and 96 parents are needed to achieve the intended power.

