### Interventions

The interventions consist of eight (for adolescents) or six (for parents) weekly sessions of 90 min, which take place in a secured chatroom (Fig. 2) with groups of three to six participants. The interventions are guided by two course leaders, one specialized health-care psychologist and one co-therapist (mostly a psychological assistant), who are trained and use a detailed manual. The training consists of three parts: 1) teaching the main principles of cognitive-behavioral group therapy and the history of the *Op Koers* courses, 2) giving more specific information on the procedures and goals related to the different sessions using examples from former chat sessions and the extensive manual for psychologists, 3) practicing in online subgroups. To ensure treatment integrity, the researcher of the coordinating hospital randomly checks the chats of participating hospitals with the manual. All participants and course leaders log on at the same time every week. Participants can log on to the homework site to view the intervention material (information sheets and videos), submit homework before every session and view additional information. Four months after the last session, there is a booster session.

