### Statistical analyses

Analyses will be performed according to the intention-to-treat principle. Primary and secondary outcomes will be assessed with linear mixed model analyses using SPSS. The intervention is qualified as effective if the intervention group improved more over time on one of the primary outcomes than the control group, at a significance level of 0.05 and at small to medium effect size d [0.2–0.5].

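### The 80% power at 84 participants makes no allowance for correlation within the chat groups, which exist in the intervention arm only

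*Protocol article*

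**What the plan says.** Participants in each trial are randomised individually within cohorts (Randomization). Those allocated to the intervention are then treated in a chatroom "with groups of three to six participants", each group led by two course leaders (Interventions). The Randomization section fixes the scale: "With an average of five participants per intervention group, a total of ten intervention groups for both adolescents and parents will be given". Exchange between group members is described as an important part of the programme, and in the parent version the parents shape what each session covers (Background; the section on the parent intervention). The waitlist arm receives usual care and has no groups (Study design).

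The Sample size section states its inputs: "Based on a design with four repeated measurements and a within subject correlation of .5", an aim "to detect an intervention effect of medium size (d = .05) over time", and "at a two-sided .05 significance level and 80% power". From these it concludes that "84 adolescents and 84 parents are needed – 42 in each condition". It then adds: "Taking into account a dropout of 15% over time, 96 adolescents and 96 parents are needed to achieve the intended power". No ICC, design effect or other allowance for chat groups appears.

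On the analysis, the article says: "Primary and secondary outcomes will be assessed with linear mixed model analyses using SPSS". It does not list the random effects. Effectiveness is judged at the 0.05 level on any one of the primary outcomes (Statistical analyses).

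**The concern.** Randomising individuals and then treating one arm in groups gives a partially nested design. People who share a chat group share leaders, discussion and timing, so their outcomes may be correlated. Waitlist participants have no such link. Positive correlation inflates the variance of the intervention-arm mean by 1 + (m − 1) × ICC for groups of size m.

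Two things are at stake. First, a sample size computed as if everyone were independent overstates the power. Second, an analysis that ignores chat group understates the standard error and rejects a true null hypothesis too often. The second matters because a result below 0.05 on a single primary outcome is enough to call the intervention effective, and the Discussion ties implementation to significant effects.

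**Working it through.** **Inputs from the article.** Two-sided alpha .05; power 80%; four measurements (baseline and three later ones); within-subject correlation .5; 42 per arm; ten groups averaging five. The effect size is printed as d = .05 but described as medium. Taken literally, .05 would need 8,374 participants under the method below, so 0.5 is used.

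**Reproducing 84.** In SD units, the mean of the three post-baseline measures has variance v = (1 + 2 × .5)/3 = 0.667. The mean change from baseline has the same variance. Then SE² = 2 × 0.667/42 = 0.03175 and SE = 0.178. Power = Φ(0.5/0.178 − 1.96) = 80.1%, with 42 per arm the smallest number that reaches 80%. Other simple readings do not return 84: one measure gives 126, the mean of all four gives 80, and a baseline-adjusted mean of three gives 54. So 84 corresponds to independent participants with nothing reserved for groups.

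The dropout inflation offers no reserve: 96 × 0.85 = 81.6 analysed, which gives about 79% power even at an ICC of zero.

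**Adding the chat groups.** With design effect DE in the intervention arm only:

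- SE² = (0.667/42) × (DE + 1)
- power = Φ(0.5/SE − 1.96)
- type I error if groups are ignored = 2 × [1 − Φ(1.96/√((1 + DE)/2))]

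Two conventions for the ICC are reasonable:

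- ICC of the averaged outcome: DE = 1 + (m − 1) × ICC
- ICC at a single visit, with a group effect constant over the three later visits: DE = 1 + (m − 1) × ICC/0.667

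Two group sizes are also reasonable: the planned average m = 5, or m = 42/10 = 4.2 analysed per group.

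Worked example (averaged outcome, m = 5, ICC .05): DE = 1.20; SE² = 0.01587 × 2.20 = 0.0349; SE = 0.187; power 76.3%; type I error if groups are ignored 6.2%.

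| Assumed ICC | Averaged, m = 4.2 | Averaged, m = 5 | Per visit, m = 4.2 | Per visit, m = 5 |
|---|---|---|---|---|
| Power, .01 | 79.5% | 79.4% | 79.2% | 79.0% |
| Power, .05 | 77.0% | 76.3% | 75.5% | 74.4% |
| Power, .10 | 74.1% | 72.6% | 71.2% | 69.2% |
| Type I error if ignored, .05 | 5.9% | 6.2% | 6.4% | 6.8% |
| Type I error if ignored, .10 | 6.9% | 7.4% | 7.8% | 8.6% |

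**Check by simulation** (40,000 runs; ten groups totalling 42 against 42 individuals; averaged-outcome ICC). A test ignoring groups rejected a true null in 5.9% of runs at ICC .05 and 6.9% at .10. A Welch test on group means stayed near 5% (4.9% and 5.1%). Its power was 73.7% and 70.3%, and 77.1% at an ICC of zero. Having only about ten groups therefore costs a few further points beyond the table, through the degrees of freedom.

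**The case against.** Four arguments count against a harsher reading.

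*The model is not specified.* A reader might infer that the planned analysis is anti-conservative. The article does not support this. It names a linear mixed model without listing random effects, and such a model can hold a chat-group term. That detail is commonly left to a full protocol or analysis plan, and neither is shown. This objection stands, so the type I error figures describe only what would follow if the term were left out.

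*The ICC is unknown.* A reader might also infer that the trial falls materially short of 80% power. At an ICC of .01 the loss is about one point, and nothing in the article shows that the ICC reaches .05. Trained leaders, a detailed manual, checks of the chats and a set subject for every parent session all limit group differences. This also stands as to size. It does not make the ICC zero, which is what the 80% requires.

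*The convention matters.* The lowest figures use a per-visit ICC and five analysed per group, which with 42 analysed implies 8.4 groups, not ten. This is why ranges are given here.

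*Baseline adjustment could recover power.* At a correlation of .5, adjusting for baseline lowers v to 0.667 − 0.25 = 0.417. Power at 42 per arm is then about 94% at an ICC of zero, 89% at .05 and 83% at .10 (per visit, m = 5). This is fair as to what the trial may achieve. But it is not the calculation that yields 84, and it does nothing for type I error.

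**Conclusion.** The point holds as a gap in the stated calculation: 84 participants give 80% power only with a chat-group ICC of zero, in a design where one arm is treated in groups whose interaction is part of the treatment. Under the calculation that reproduces 84, power is about 79% at ICC .01, 74–77% at .05 and 69–74% at .10. If chat group were left out of the model, type I error would be about 5.9–6.8% at .05 and 6.9–8.6% at .10.

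These figures rest on d = 0.5, 42 analysed per arm, an assumed ICC and waitlist participants treated as independent. The last of these sets aside couples who both join the parent trial.

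The article supports neither the claim that the analysis ignores chat group nor the claim that the power loss is large. This is a should-fix, not a must-fix.

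**What to change.** In Statistical analyses, specify a random effect for chat group in the intervention arm only, coding each waitlist participant as a group of one, with Satterthwaite or Kenward-Roger degrees of freedom. Settle this before outcomes are analysed, so that the choice cannot depend on the results.

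In Sample size, state that the 80% assumes a chat-group ICC of zero. Give the power at 84 over an assumed ICC range, naming the convention used (per visit or averaged outcome, and the number analysed per group).

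The cost is one model term and one restated figure, with no extra participants. The stated power becomes less favourable and intervals slightly wider, partly because about ten groups leave few degrees of freedom. The group term protects the type I error but does not restore the lost power.

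### The planning effect is printed as d = .05 but called medium; the stated 84 participants per trial fit d of about 0.5, so the printed figure is almost certainly a decimal-point error

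*Protocol article*

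**What the plan says.** The Sample size section of the protocol article starts from prior evidence: earlier studies of the programme and "comparable effect studies showed effects of medium size". It assumes "four repeated measurements and a within subject correlation of .5" and plans "at a two-sided .05 significance level and 80% power". On that basis it states that "84 adolescents and 84 parents are needed", that is "42 in each condition", to detect an "intervention effect of medium size (d = .05) over time". The same figures serve both the adolescent and the parent trial. Allowance for dropout then raises each trial to 96.

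The Statistical analyses section gives the article's only other figures on the d scale. An intervention counts as effective if it does better than control on one of the primary outcomes, at the .05 level and "at small to medium effect size d [0.2–0.5".

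**The concern.** A d of .05 cannot be a medium effect on the article's own scale. That scale starts at 0.2 for small, so the printed value is a quarter of small (.05/0.2 = 0.25) and a tenth of 0.5, the upper end of the range.

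The effect size is the input on which the sample size and the 80% power rest, and it is the only numerical planning effect given for either trial. If the printed value is taken literally, the power statement is wrong for both trials. Anyone who copies the planning effect into a review or a later protocol copies a value ten times too small, and the trials appear far more sensitive than they are.

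**Working it through.** **Inputs.** From Sample size: four measurements, within-subject correlation ρ = .5, two-sided α = .05, power 80%, 42 per arm, printed effect d = .05. From Statistical analyses: small to medium runs from 0.2 to 0.5.

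**Assumptions.** The article names no formula. I assume equal variances and equal correlations between all time points (compound symmetry), and a comparison of arms on an average of the repeated measurements.

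**Formula.** n per arm = 2 × (1.960 + 0.842)² × v / d², where v is the variance of the averaged outcome relative to a single measurement:
- mean of the three post-baseline measurements: v = (1 + 2 × .5)/3 = 0.667
- that mean minus baseline: v = 0.667 + 1 − 2 × .5 = 0.667, the same value because ρ = .5
- mean of all four measurements: v = (1 + 3 × .5)/4 = 0.625

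**Step 1. Can the stated 84 be reproduced?** Results at each value of d (normal approximation, rounded up per arm):

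| Averaged outcome | v | d = 0.5: n per arm | d = 0.5: total | d = .05: n per arm | d = .05: total |
|---|---|---|---|---|---|
| Post-baseline mean, or its change from baseline | 0.667 | 41.9, so 42 | 84 | 4,187 | 8,374 |
| Mean of all four | 0.625 | 39.2, so 40 | 80 | 3,925 | 7,850 |

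Using the t distribution at d = 0.5, the totals are 86 and 82. So d = 0.5 gives 80 to 86, which brackets the stated 84. The printed d = .05 gives totals larger by (0.5/.05)² = 100 before rounding.

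**Step 2. Power of 42 per arm at d = .05** (post-baseline mean):
- standard error = √(0.667 × 2/42) = 0.178
- d / standard error = .05/0.178 = 0.281
- two-sided power = Φ(−1.960 + 0.281) + Φ(−1.960 − 0.281) = 0.047 + 0.013, about 5.9%

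The mean of all four measurements also gives about 6%, and so does 48 per arm (96/2).

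**Step 3. Power of 42 per arm at d = 0.5.** It is 79% to 83% across the two averages and the normal and t versions. The smallest effect detectable with 80% power is 0.48 (mean of four) to 0.50 (post-baseline mean).

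**Step 4. Does another formula rescue d = .05?** Single time point, change score, ANCOVA, linear slope and the repeated-measures F tests were also tried. Power at d = .05 with 84 participants stayed between 5.6% and 7.5%. Among the mean-difference formulas the smallest total for 80% power was about 5,200 (ANCOVA on the post-baseline mean).

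**The case against.** The strongest reply is that the article resolves the slip itself. It cites medium effects in earlier studies, calls its own target medium, ends its d range at 0.5, and states a sample size that fits about 0.5. No analysis or decision rule uses .05 as an effect size. This stands, and it limits the consequence: the number of participants was evidently derived from about 0.5. It does not make the printed value right, because that value is the stated basis for the power.

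Three stronger readings are tempting, and the article does not support them.

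- A reader might infer that the trials have 6% power, or need a hundred times more participants. That treats the misprint as the value actually used in planning, which the stated 84 contradicts.
- A reader might infer that 84 follows only from d = 0.5, and only from the post-baseline mean compared with baseline. At ρ = .5 the plain post-baseline mean and its change from baseline both give 42 per arm, so the figures cannot tell them apart. Other formulas at d = 0.5 give other totals: 126 for a single time point, 104 to 114 for a slope, 54 for ANCOVA on the post-baseline mean and 24 for the group-by-time interaction F test. The exact match with 84 therefore does not identify the contrast, and a condensed article may leave that to the full protocol.
- A reader might take a later null result as excluding effects of .05. That would overlook the word medium in the same phrase, and such exclusion would have to come from a confidence interval, not from a planning figure.

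Whether a success criterion that begins at 0.2 suits trials planned around 0.5 is a separate question. It does not follow from the misprint and adds nothing to this point.

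**Conclusion.** The printed planning effect is wrong as written. It disagrees with its label, with the range under Statistical analyses and with the stated sample size. At d = .05, 42 per arm has about 6% power (5.6% to 7.5% over every formula tried), and 80% power would need roughly 8,000 participants per trial under the averaged formulas. At d of about 0.5 the same averaged formulas give 80 to 86 participants.

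That the printed .05 is incompatible with 84 does not depend on the formula. That 0.5 was intended is an inference from the wording, the range and the averaged repeated-measures formulas under compound symmetry. It is a strong inference, but the original calculation is not shown. On that reading the planned sample size stands, and the error lies in the reporting of the design rather than in the design.

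**What to change.** Retrieve the original sample size calculation and confirm the effect size used. Then correct d = .05 to d = 0.5 in the Sample size section; the correction applies to both trials. If the contrast behind the 42 per arm is reported as well, take it from that calculation and do not assume it to be the mean of T1 to T3 against T0. The cost is one text correction, with no change to recruitment, conduct or analysis.

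### Enrolling 96 per trial allows for 12.5% dropout, not the stated 15%: 96 × 0.85 = 81.6 against a requirement of 84

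*Protocol article*

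**What the plan says.** All the figures stand in the Sample size section of the protocol article. The requirement before dropout is "84 adolescents and 84 parents are needed – 42 in each condition", set "at a two-sided .05 significance level and 80% power". It rests on four measurements and a within-subject correlation of 0.5. The next sentence raises the number for attrition: "Taking into account a dropout of 15% over time, 96 adolescents and 96 parents are needed to achieve the intended power".

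The Randomization section makes the two arms equal in size, so 96 means 48 per arm. On capacity it says: "With an average of five participants per intervention group, a total of ten intervention groups for both adolescents and parents will be given". The Statistical analyses section specifies intention to treat and linear mixed models. The article gives no other dropout rate and no formula for the inflation.

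**The concern.** The 96 is presented as the number that secures the intended power after 15% dropout. A reader who checks it finds that it leaves fewer than 84. The three printed numbers (84, 15%, 96) cannot all be right together, whatever effect size or variance model lies behind the 84.

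What is at stake is the recruitment target of two trials. The 84 carries almost no margin above 80% power, so any shortfall in completers takes a completers-only calculation below the stated level. The Discussion also names recruitment in the adolescent trial as a threat to statistical power, so the target should be correct as stated.

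**Working it through.** **Inputs (Sample size section, with equal arms from the Randomization section).** Required N = 84, or n = 42 per arm; dropout 15%; enrolled 96, or 48 per arm; two-sided alpha 0.05; power 80%; correlation 0.5; four measurements.

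**1. Reproducing the 84.** The article does not say which formula was used, and it prints the effect size as 0.05 while calling it medium. I assume d = 0.5. For the mean of three post-baseline measures at correlation 0.5, in standard deviation units:

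- v = (1 + 2 × 0.5)/3 = 0.667
- n per arm = 2 × (1.960 + 0.842)² × v/d² = 2 × 7.85 × 0.667/0.25 = 41.9, so 42, and 84 in total

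This matches the printed requirement. A change from baseline to that mean has the same variance and gives the same 84. With d = 0.05 the same model needs 8,374, so 0.5 is the workable reading. Step 2 does not depend on this choice.

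**2. The dropout allowance.**

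- Completers from 96: 96 × 0.85 = 81.6, or 40.8 per arm. That is 2.4 below 84.
- Dropout that 96 can absorb: 1 − 84/96 = 12.5%.
- Enrolment needed: 84/(1 − 0.15) = 98.8, so 99.
- With equal arms: 42/0.85 = 49.4, so 50 per arm and 100 in total. Check: 100 × 0.85 = 85, which is at least 84.
- Shortfall: 3 participants per trial, or 4 with equal arms.

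No rounding turns 98.8 into 96. For comparison, 84 × 1.15 = 96.6 and 42 × 1.15 = 48.3.

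**3. Power if dropouts give no follow-up data.** Power = Φ(d/SE − 1.960), with SE = √(2v/n):

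| n per arm | SE | Power |
|---|---|---|
| 42 | 0.1782 | 80.1% |
| 40.8 | 0.1808 | 79.0% |

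A t-based calculation gives 79.2% and 78.0%, so the difference of about one percentage point is the same.

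**4. Power if some dropouts contribute follow-up data.** In the same model a participant with one, two or three post-baseline visits has variance 1, 0.75 or 0.667, and therefore information 1, 1.333 or 1.5. The number of completers per arm to which 48 enrolled are equivalent is then:

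| Timing of the 15% (assumed) | Equivalent completers per arm | Power |
|---|---|---|
| All before T1 | 48 × 0.85 = 40.8 | 79.0% |
| A quarter of dropouts (3.75% of those enrolled) give T1 only | 48 × (0.85 × 1.5 + 0.0375 × 1)/1.5 = 42.0 | 80.1% |
| 5% before each of T1, T2 and T3 | 48 × (0.85 × 1.5 + 0.05 × 1 + 0.05 × 1.333)/1.5 = 44.5 | 82.4% |
| All after T1 | 48 × (0.85 × 1.5 + 0.15 × 1)/1.5 = 45.6 | about 83% |

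These rows assume a constant effect across follow-up visits and ignorable missingness. The article does not state when dropout is expected.

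**The case against.** The strongest reply is that dropout is described as occurring over time, in a design with three follow-up assessments analysed by mixed models. A participant lost after T1 or T2 still contributes. In the model above, 96 gets back to about 80% power once a quarter of the dropouts provide T1. This stands. A reader might infer from the headcount that neither trial reaches its intended power; the document does not support that, because the loss appears only when nearly all dropouts leave before T1.

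The reply does not rescue the sentence itself. The Sample size section takes no credit for partial data. It treats dropout as a loss from 84 and inflates for it, and the inflation is too small for the rate stated.

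Three further inferences also go too far:

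- **Cause.** The 96 is consistent with multiplying by 1.15 and rounding down. No formula is given, so this is only a plausible origin, and the point does not need it.
- **Compounding.** A reader might add this loss to losses from clustering in the groups and from multiple primary outcomes. Nothing calculated here supports that. The success rule in Statistical analyses accepts one primary outcome at 0.05 with no stated correction, so as written multiplicity costs no power.
- **Capacity.** Enrolling 100 needs no extra groups only if ten groups are meant for each trial. The wording could also be read as ten groups across both trials. That would give about 25 intervention places per trial, too few even for the planned 48, so the first reading fits better, but the text does not settle it.

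**Conclusion.** The enrolment target does not follow from its own inputs, in either trial. This rests only on the printed 84, 15% and 96, and is certain: 96 covers 12.5% dropout, and 15% calls for 99, or 100 with equal arms.

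The consequence is minor: 3 or 4 participants per trial and at most about one percentage point of power, from 80.1% to about 79.0%. Those power figures assume d = 0.5, the mean of three post-baseline measures at correlation 0.5, and no follow-up data from any dropout. With some T1 or T2 data from dropouts, the loss shrinks or disappears. It is a wrong figure to correct, and it does not show that either trial is underpowered.

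**What to change.** Correct the sentence in the Sample size section, for both trials, in one of these ways:

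1. Keep 96 and say that it allows for 12.5% dropout.
2. Keep 96 and 15%, and say that about 82 participants are then expected to complete, with about 79% power in the worst case where dropouts contribute no follow-up data. State the effect size and variance model behind that figure.
3. State 100 per trial, 50 per arm.

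The first two cost one sentence and leave recruitment unchanged, which makes restating the figure the cleaner choice. The third adds 4 participants per trial. It fits the planned places (10 × 5 = 50) if the Randomization section means ten groups of about five for each trial, and that section should then say so.
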